## INTRODUCTION

Parkinson's disease (PD) is a progressive, neurodegenerative clinical condition with increasing prevalence worldwide.(AASETH et al., 2018; BLOEM et al., 2021)Among the major neurological disorders, PD is the one that is growing most rapidly in prevalence, disability, and mortality.(GBD, 2017)According to the Global Burden of Disease Study, it is estimated that by 2040 the number of individuals diagnosed with PD will be approximately 13 million worldwide.(GBD, 2017; RAY DORSEY et al., 2018)This number represents double the number of cases recorded in 2015.GBD, 2017; RAY DORSEY et al., 2018)This indicates a rapid increase in the incidence and duration of the disease. This increase has been mainly associated with the rising rate of population aging.(RAY DORSEY et al., 2018)Therefore, advances in clinical research related to PD disorders are essential.

Recent studies on the pathogenesis of PD indicate that the onset of this health condition is associated with the abnormal deposition of protein aggregates rich in  $\alpha$ -synuclein, called Lewy bodies, in the central nervous system.(BORGHAMMER, 2018; CÓPPOLA, 2018; RAZA et al., 2019)According to the staging scheme proposed by Braak et al. (2003), the first staging sites for PD are commonly the olfactory bulb, dorsal motor nucleus of the vagus nerve, and the lower region of the brainstem.(BORGHAMMER, 2018; BRAAK et al., 2003)Subsequently, the monoaminergic pontine nuclei and dopaminergic neurons of the substantia nigra are affected.(BORGHAMMER, 2018; BRAAK et al., 2003)This staging scheme explains the clinical evolution of PD, characterized by the initial appearance of non-motor symptoms that include alterations such as sleep disorders, hypothyroidism, and constipation.(SCHAPIRA et al., 2017).

The main motor symptoms of PD are known as cardinal signs and refer to resting tremor, bradykinesia, rigidity, and postural instability.(AASETH et al., 2018; SCHAPIRA et al., 2017). Those symptoms are predominantly caused by the loss of dopaminergic neurons in the substantia nigra pars compacta of the central nervous system.(SCHAPIRA et al., 2017) Therefore, one of the most used pharmacological therapeutic strategies in the treatment of PD is dopamine replacement, through the oral administration of the drug levodopa. (POEWE et al., 2020; SCHAPIRA et al., 2017)According to the diagnostic criteria adopted by The United Kingdom PD Society, the diagnosis of PD should be made in three stages: 1) Diagnosis of Parkinsonian

syndrome: presence of bradykinesia associated with another symptom among the cardinal signs. 2) Exclusion of other diagnoses that may cause Parkinsonian syndrome, such as stroke or traumatic brain injury. 3) Presence of three or more supporting criteria such as unilateral onset, resting tremor, progression of symptoms, and improvement of symptoms with the use of Levodopa.(MARSILI et al., 2018)As the disease progresses, Levodopa doses are commonly increased, resulting in periods known as the "on period," during which motor symptoms are attenuated, and the "off period," during which motor symptoms reappear.(SCHAPIRA et al., 2017)However, even with pharmacological treatment measures, the natural course of the disease results in the progressive decline of various functions in patients with PD, including mobility.(BOUCA-MACHADO et al., 2018; TOMLINSON et al., 2014)In these individuals, the decline in mobility compromises the ability to move safely in different environments and commonly becomes noticeable with a reduction in walking speed, usually the first sign of gait changes observed in this population.(BOUCA-MACHADO et al., 2018).

Individuals with PD commonly present with reduced gait speed, decreased step length, limb asymmetry, decreased upper limb balance, increased base of support and cadence, and reduced postural balance during gait.(DI BIASE et al., 2020; MIRELMAN et al., 2019)Furthermore, individuals with PD may exhibit hesitancy to initiate walking and episodes of freezing, characterized by a sudden, transient cessation of voluntary motor activity.(DI BIASE et al., 2020; MIRELMAN et al., 2019)As the disease progresses, altered gait patterns may also worsen, affecting mobility, independence, and quality of life for these individuals.(DI BIASE et al., 2020; MIRELMAN et al., 2019).

A strategy commonly used in an attempt to improve the mobility of individuals with PD during gait requires the prescription of assistive devices, such as canes and walkers.(BRYANT et al., 2014)The use of these devices increases the base of support for individuals, allowing for a greater range of movement of the center of mass during gait.(BRYANT et al., 2014)Therefore, it is believed that the use of these devices can improve balance, confidence, and reduce falls during walking.(BRYANT et al., 2014; KADER et al., 2018)Furthermore, the use of these devices, as well as the perceived need for their use, tends to increase among individuals with PD over the years.(KADER et al., 2018)However, the prescription of these devices is based solely on the clinical judgment of healthcare professionals, and no scientific guidelines or recommendations for the use of assistive devices for individuals with PD were found.(BRYANT et al., 2014).

In a study conducted with 85 individuals with PD, Bryant and colleagues (2014) identified that 36.6% of individuals used assistive devices while walking, with the cane being the most common device.(BRYANT et al., 2014)Furthermore, it was identified that 56.8% of individuals who took more than 13 seconds to complete the five-meter Timed Up Go test regularly used assistive devices. Among individuals who regularly used such devices, 77.8% showed lower levels of confidence in their balance.(BRYANT et al., 2014)However, the authors did not compare the individuals' performance in walking activities with and without a cane.(BRYANT et al., 2014)Furthermore, the study did not consider the average time the device was used by the individuals who reported using it.(BRYANT et al., 2014).

Other studies have focused on investigating the effects of using assistive devices during gait in patients with PD.(KEGELMEYER et al., 2013)Kegelmeyer et al. (2013) investigated the influence of the use of different assistive devices on gait patterns in 27 individuals with PD.(KEGELMEYER et al., 2013) According to the authors, only the use of the four-wheeled walker reproduced gait patterns similar to gait without the device.(KEGELMEYER et al., 2013)For the other devices evaluated (single-point cane, standard walker, and two- and six-wheeled walkers), their use decreased walking speed for all individuals.(KEGELMEYER et al., 2013)Furthermore, the use of these devices was associated with decreased step length, decreased base of support, increased double support time, and decreased swing phase during gait.(KEGELMEYER et al., 2013).

In another study, conducted by Bryant et al. (2012), 10 individuals with PD were evaluated during gait without an assistive device, with a single-point cane, and with a walker.(BRYANT et al., 2012)The authors reported that the use of the devices decreased walking speed.(BRYANT et al., 2012)Furthermore, the use of a walker decreased step length during gait. In a study conducted by Cubo et al. (2003), 19 individuals with PD were evaluated in gait activities without the use of assistive devices, gait with a standard walker, and gait with a wheeled walker.(CUBO et al., 2003)The authors compared walking time, the number and duration of freezing episodes, and the average duration of freezing.(CUBO et al., 2003).The authors found that walking speed was higher without the use of the devices.(CUBO et al., 2003)Furthermore, the use of standard walkers significantly increased the number and duration of freezing episodes.(CUBO et al., 2003).

Although the results of the aforementioned studies indicate that the use of walking aids may worsen gait patterns in individuals with PD, all studies investigated the immediate effects of using such devices, since individuals received instructions and were

familiarized with the devices only a few minutes before the assessment measures.(BRYANT et al., 2012; CUBO et al., 2003; KEGELMEYER et al., 2013)Thus, despite being commonly prescribed in clinical practice, the effects of training and use of assistive devices, including single-point canes, on gait speed in individuals with PD are poorly understood.

## **OBJECTIVES**

### **2.1 Primary objective**

The primary objective of this project will be to investigate the effect of cane training and use on gait speed in individuals with PD.

### **2.2 Secondary objectives:**

The secondary objectives will be: to investigate the effect of training and cane use on cadence, step length, gait confidence, mobility, freezing of gait in individuals with PD, and to investigate the satisfaction of individuals with PD about the cane use.

## **MATERIALS AND METHODS**

### **Outline**

This is a randomized clinical trial with blinded assessors. The study will be submitted to the Research Ethics Committee of the Federal University of Minas Gerais, and the study protocol will be registered in [the relevant directory/institution].[www.ClinicalTrials.gov](http://www.ClinicalTrials.gov)The study will follow the Consolidated Standards of Reporting Trials (CONSORT) guidelines.(CUSCHIERI, 2019).

### **Participants**

Individuals diagnosed with PD will be recruited from the community in the city of Belo Horizonte, Minas Gerais, Brazil. Recruitment will be done through patient lists from other projects with the same population, as well as through outreach on social media, hospitals, primary health care units, and university spaces. Individuals who meet the following criteria will be included.: age  $\geq 40$  years; PD diagnosis confirmed by a neurologist; Classification of II to IV in the Hoehn & Yahr (HY) Disability Stages(GOULART et al., 2005) use of anti-Parkinsonian medication and medical stability for at least 6 months; ability to walk independently in a 14-meter corridor at a walking speed equal to or less than 1.1 m/s; ability to use a single-point cane correctly and safely

while walking without prior use of assistive devices. To assess the individual's ability to use the cane, the following criteria will be adopted: 1) absence of visual, cognitive, physical, or auditory impairment that prevents training and use of the device; and 2) absence of loss of balance while walking with the device.(KEGELMEYER et al., 2013; MCCANDLESS et al., 2016)Individuals with cognitive impairment, as assessed by the Mini-Mental State Examination.(BRUCKI et al., 2003)or that present any other neurological, cardiopulmonary, or musculoskeletal condition that may compromise the performance of the tests will be excluded.

### **Randomization**

Individuals will be randomly assigned to the experimental and control groups. The allocation ratio will be 1:1, according to a randomization plan generated by a website. The randomization sequence will be kept in sealed opaque envelopes. The envelopes will be prepared before the start of the study by a research assistant not involved in the study.

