### **Sample calculation**

Twenty-six individuals will be included in this study. The sample size calculation was performed considering the clinically important difference in the primary outcome measure, gait speed. (Hass et al., 2014)Considering a significance level ( $\alpha$ ) of 5% and a

power of 0.80, an  $n=9$  was found for each group. Therefore, a sample size of 18 individuals. Assuming a sample loss of 30% of individuals throughout the study, a total sample of 26 individuals was determined, with 13 in each group.

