**12. March**

0 = Normal

1. The gait is slow, the feet may drag, and the steps may be short, but there is no propulsion or festination.

2 = Walks with difficulty, but needs little or no help; there may be some festination, short steps, or propulsion.

3 = Severe gait disorder requiring assistance.

4. Marching is impossible, even with assistance.

**13. Postural stability (Observe the response to a sudden backward displacement, caused by a push on the shoulders, with the patient standing with eyes open and feet slightly apart. Warn the patient beforehand)**

0 = Normal

1 = Retropulsion, although recovery occurs without assistance.

2 = Absence of postural reflex; could have fallen if the evaluator had not prevented it.

3 = Very unstable; tendency to lose balance spontaneously.

4 = Unable to stand without assistance.

**14. Bradykinesia and hypokinesia. (Combination of slowness, indecisiveness, decreased arm swing, reduced range of motion, and general scarcity of movement).**

0 = Absent

1 = Minimal slowness, giving the movement a decisive character; this could be normal in some people. Amplitude possibly reduced.

2 = Mild degree of slowness and scarcity of movements; clearly abnormal. There may be a decrease in amplitude.

3 = Moderate slowness, poor movement, or reduced range of motion.

4 = Marked slowness and poverty of movement with reduced amplitude of movements.

|                                                             |
|-------------------------------------------------------------|
| - Hoehn and Yahr Disability Stages Scale (modified): |
|-------------------------------------------------------------|

|                                    |
|------------------------------------|
| 0: Absence of signs of the disease |
|------------------------------------|

|                        |
|------------------------|
| 1.0: Unilateral change |
|------------------------|

|                                                   |
|---------------------------------------------------|
| 1.5: Unilateral alteration with axial involvement |
|---------------------------------------------------|

|                                                     |
|-----------------------------------------------------|
| 2.0: Bilateral alteration, without balance deficit. |
|-----------------------------------------------------|

|                                                                |
|----------------------------------------------------------------|

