| 2.5: Mild bilateral alteration with recovery in the push test. |
|----------------------------------------------------------------|

|                                                                                                |
|------------------------------------------------------------------------------------------------|
| 3.0: Mild to moderate bilateral alteration, some postural instability, physically independent. |
|------------------------------------------------------------------------------------------------|

|                                                                         |
|-------------------------------------------------------------------------|
| 4.0: Severe disability, still able to walk or stand without assistance. |
|-------------------------------------------------------------------------|

|                                                     |
|-----------------------------------------------------|
| 5.0: Confined to bed or wheelchair unless assisted. |
|-----------------------------------------------------|

H&Y Score: \_\_\_\_\_

**Walking speed test without a cane**(A measure after familiarization)

| Test order:                       | Time (s) | Speed (m/s) |
|-----------------------------------|----------|-------------|
| Automatically selected gear speed |          |             |
| Maximum driving speed             |          |             |

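### Disease stage is used neither to allocate nor to analyse 26 people from Hoehn & Yahr II to IV, so a chance imbalance in stage can add avoidable noise to the comparison of change

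*Combined protocol and SAP*

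**What the plan says.** The Randomization section gives the ratio and the source of the list: "The allocation ratio will be 1:1, according to a randomization plan generated by a website". It adds that the sequence sits in sealed opaque envelopes, prepared before the study starts by an assistant outside the study. It mentions no strata, block size or minimisation, and neither does any other section.

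The Participants section admits "Classification of II to IV in the Hoehn & Yahr (HY) Disability Stages". On the scale in the evaluation form (Appendix II), the lower end reads "2.0: Bilateral alteration, without balance deficit" and the upper end "4.0: Severe disability, still able to walk or stand without assistance". Procedures places the eligibility check at the initial assessment, ahead of allocation, and the form has a field for stage. Stage is therefore known in time to be used.

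Sample calculation ends with "a total sample of 26 individuals was determined, with 13 in each group", sized to leave 9 per group after loss. Data analysis specifies a repeated measures ANOVA over the initial, post-training and follow-up measurements. It names no stage, UPDRS-III or other prognostic term, and does not say which term is the test of the cane effect.

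**The concern.** A cane is chiefly a balance aid: the Introduction says that such devices widen the base of support and are believed to improve balance and confidence. Balance is also what separates stage 2 from stage 3 on the trial's own form. It is plausible, though the documents do not show it, that the course of gait over the study and the response to a cane both depend on stage.

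With 9 to 13 people analysed per arm, an allocation that ignores stage can put clearly more of the severe cases on one side. If stage affects change, a reader of that one trial could not fully separate the cane effect from the stage difference, because the planned model has no term for it. Secondly, the stated 13 per group requires some restriction on the list, and none is described.

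**Working it through.** **The plan's own figure.** 18 / (1 - 0.30) = 25.7, rounded up to 26, or 13 per arm. This agrees with Sample calculation. The 9 per group cannot be checked, because neither the difference in m/s nor its SD is stated.

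**Chance imbalance in stage.** The documents give no stage mix, so K, the number of the 26 at stage 3-4, is assumed. With a 13:13 split and no strata, the number x in one arm is hypergeometric: P(x) = C(K, x) · C(26-K, 13-x) / C(26, 13), with C(26, 13) = 10,400,600.

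For K = 8, a 6:2 or worse split in either direction has probability 2 × (28 × 31,824 + 8 × 18,564 + 1 × 8,568) / 10,400,600 = 0.202.

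| Assumed K of 26 | Gap of 4 or more people |
|---|---|
| 6 | 16% |
| 8 | 20% |
| 10 | 23% |

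The cut-off matters when K is odd, because the gap is then odd too. A gap of 3 or more has probability 32% for K = 5 and 43% for K = 13; a gap of 5 or more, 4% and 12%.

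**Shift in one realised trial.** Assume that stage 3-4 people change by 0.10 m/s less than stage 2 people. A 6:2 split then shifts the group difference in change by (6 - 2)/13 × 0.10 = 0.031 m/s.

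**Effect on precision.** Assumptions: K = 10, measurement SD 0.09 m/s at each visit, no cane effect.
- If stage affects level only, it cancels in change from baseline. The squared standard error is 2 × (2 × 0.09²)/13 = 0.00249, so SE = 0.050.
- If stage also lowers change by 0.10 m/s, unstratified allocation adds 0.10² times the variance of the between-arm difference in the stage 3-4 proportion (SD 0.195): 0.01 × 0.195² = 0.00038. The total is 0.00287, so SE = 0.054. The variance is about 15% larger (0.00287/0.00249).

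A simulation (10,000 trials per scenario, between-person SD 0.18 m/s, severe stage 0.2 to 0.3 m/s slower) agrees. For change, the SE was 0.050 with and without strata when stage affected level only, and 0.054 unstratified against 0.049 stratified when it affected change by 0.10 m/s. Without strata, mean bias was 0.001 m/s or less and type I error 4.8% to 5.2%.

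The same runs show why the model must match the allocation. With stratified allocation but no stage term, the test of change rejected in 3.3% of null trials in the largest scenario; with stage and baseline in the model, in 4.8%.

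**Arm sizes if the list is unrestricted.** Under Binomial(26, 0.5), P(exactly 13) = 10,400,600 / 2²⁶ = 0.155, and P(10:16 or more uneven) = 0.327.

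**The case against.** The strongest reply is that the trial is valid as it stands. A reader might infer that part of any group difference would be stage. The documents do not support that: in a randomised comparison chance imbalance is random error, already reflected in the standard error, and the simulated bias and error rate above confirm it. The planned ANOVA includes the initial measurement, so a lasting difference in walking level between stages drops out of the group-by-time contrast. This stands, and it confines the point to stage acting on change.

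A reader might also expect a stage stratum to balance baseline speed well. It would do so only modestly. With 8 of 26 at stage 3-4, SD 0.20 m/s and a 0.20 m/s gap between stages (all assumed), the chance of a baseline difference above 0.10 m/s falls from 20% to 15% if that SD is overall, or from about 25% to 21% if it is within stage. Baseline speed is no argument for this change.

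Three further objections have weight. The entry criteria narrow severity: independent walking at 1.1 m/s or less, no prior device, no loss of balance with the cane. The website plan may contain blocks or strata that the text omits, so silence is not proof of absence. And Procedures describes the physiotherapist who allocates as blinded to the assessment, so passing on the stratum would disclose part of it.

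On the other side, Data analysis does not name the tested term. If post-training values alone were compared, exposure would be larger: SE 0.088 to 0.111 unstratified against 0.079 stratified in the same simulation.

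**Conclusion.** The point holds as a worthwhile, inexpensive improvement, not as a flaw that invalidates the comparison. The plan describes no use of stage in allocation or analysis, although stage is available beforehand and the range is wide for 26 people. A gap of 4 or more stage 3-4 people has a 16% to 23% chance for 6 to 10 such people. It matters only if stage affects change over time or response to the cane; then a 6:2 split moves the result by about 0.03 m/s and the standard error rises from about 0.050 to 0.054. The stage mix, the 0.10 m/s effect and the SDs are assumptions. Because the plan states no target difference in m/s, the shift cannot be set against it. The 15% figure for 13:13 applies only if the list is unrestricted; the firm point there is that the sequence method is not reported.

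**What to change.** - **Randomization:** state how the sequence is generated. Use permuted blocks of randomly varied size within one two-level stratum, Hoehn & Yahr 2-2.5 and 3-4, with one numbered envelope set per stratum. Use no second factor; with 26 people the strata would become sparse.
- **Data analysis:** include that stratum as a between-person factor, with its interaction with time, since that is the term that absorbs a stage effect on change. Name the group-by-time contrast as the test.
- **If the envelopes are already prepared:** leave the allocation alone, report how the list was made, and prespecify Hoehn & Yahr stage as a covariate.

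No extra patients are needed, but the change is not free. The stage term takes one degree of freedom in a comparison of change at one visit (two for stage-by-time over three visits). The last assignment in a block is slightly easier to guess, which varied block sizes limit. Final blocks may stay incomplete, so 13:13 becomes approximate. To keep the allocating physiotherapist blinded to the assessment, the independent assistant can receive the stratum from the assessor and hand over the next envelope without showing which set it came from.
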